### Statistical methods

Data will be analyzed using SPSS version 19.0 (SPSS 19.0, SPSS Inc., Chicago, IL, USA) by two qualified statisticians. Full analysis set (FAS), per-protocol analysis set (PPS), and safety set (SS) principles will be used to evaluate the final results. FAS is determined according to an intention-to-treat (ITT) population and includes all patients who have received at least one treatment. PPS will include all patients with good compliance who have completed the entire intervention. SS will include all patients who have received at least one intervention. The results of the measurement data analysis will be described using mean, median, 25th percentile, 75th percentile, standard deviation, maximum values, and minimum values. The comparison between the groups will be performed using the independent sample *t*-test or the Mann-Whitney *U* rank sum test according to whether the measurement data show a normal distribution and homogeneous variance. Frequency and constituent ratios will be used to describe enumeration data, and Pearson’s *χ*^2^ test or Fisher’s exact test will be used for group comparisons. Pearson correlations and Spearman correlations will be used to analyze the correlations between different indicators. All statistical tests will be considered statistically significant at *P <* 0.05 with a two-sided test. The gut microbiome will be analyzed using metagenomic analysis by BGI Shenzhen Co., Ltd (China).

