#### Acupuncture treatment

Acupuncture points will be selected based on the Zang-fu organ system, Yin-Yang theory, and clinical rules for PCOS acupoint selection. Two sets of acupoints will be used; each set will be used on alternate treatments. The first acupoint formula comprises DU-20, DU-24, GB-13, RN-12, ST-25, RN-4, EX-CA-1, KI-12, SP-6, and LR-3. The second acupoint formula comprises BL-23, BL-32, SP-6, and KI-3. Disposable, single-use, sterilized needles (Huatuo, Suzhou Medical Appliance Fact. 215005 Suzhou, China) of sizes 0.25 mm × 25 mm, 0.25 mm × 40 mm, and 0.25 mm × 50 mm will be inserted into the acupoints, and a *Deqi* sensation obtained by manipulating the needles. Table 2 shows the location, depth, and type of insertion for each acupoint. Each treatment will last for 30 min; no manipulation will be used once the *Deqi* sensation is achieved. The acupuncture treatment will be conducted three times a week from the fifth day of menstruation or withdrawal bleeding until the start of the next menstruation, for up to three menstrual cycles.

**Table 2 Tab2:** Acupuncture protocol

Acupoints	Location	Method

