### Randomization and allocation concealment

Patients will be randomly assigned to the study group or control group in a 1:1 ratio using a random number table. The random numbers will be provided by an independent statistician using the SPSS statistical software (version 19.0, SPSS Inc., Chicago, IL, USA). Random numbers and treatment protocols will be placed in sealed envelopes by an independent investigator. When a patient is enrolled, acupuncturists will check whether the envelope is sealed and then open the envelope to find the random number and treatment protocol for the patient.

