### Blinding

As this is an open-label trial, neither the patients nor the acupuncturists will be blinded for the treatment. However, to eliminate potential bias, other researchers (including data collectors and statisticians) will be blinded.

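### The full analysis set is labelled intention-to-treat but excludes randomised patients who never start treatment, so no defined set holds everyone randomised and the open-label comparison can be biased.

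*Protocol article*

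**What the plan says.** The Statistical methods section of the protocol article defines three analysis sets:

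- Full analysis set (FAS): "FAS is determined according to an intention-to-treat (ITT) population and includes all patients who have received at least one treatment".
- Safety set: "SS will include all patients who have received at least one intervention".
- Per-protocol set: "PPS will include all patients with good compliance who have completed the entire intervention".

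Four other sections bear on the point:

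- Blinding: "As this is an open-label trial, neither the patients nor the acupuncturists will be blinded for the treatment". Other researchers, including data collectors and statisticians, are to be blinded.
- Randomization and allocation concealment: "When a patient is enrolled, acupuncturists will check whether the envelope is sealed and then open the envelope".
- Acupuncture treatment: sessions run "from the fifth day of menstruation or withdrawal bleeding until the start of the next menstruation". Clomiphene also starts on day 5, and patients with amenorrhea begin after a bleed induced by progestin.
- Data collection and management: withdrawals and their reasons will be reported, and dropouts are to be kept in the analysis by imputation.

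**The concern.** An intention-to-treat set is fixed by randomisation alone. The FAS sentence invokes that principle and then makes entry depend on something that happens afterwards.

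Leaving out patients who never start does little harm when the decision not to start cannot depend on the assigned arm, as under effective blinding. That protection is absent here, because both patient and acupuncturist know the arm. The arms also differ in burden and appeal: acupuncture three times a week plus clomiphene, against clomiphene alone. A study-group patient may decline the visits, and a control may leave because she hoped for acupuncture. If those who leave differ in prognosis from those who stay, the treated-only groups are no longer the groups that randomisation formed. The result would nevertheless be reported under an intention-to-treat label.

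**Working it through.** **1. The definitions side by side**

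| Set | Entry rule | Contains all randomised? |
|---|---|---|
| FAS | at least one treatment | No |
| Safety set | at least one intervention | No |
| Per-protocol | good compliance, intervention completed | No |

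The FAS and the safety set have practically the same membership. The FAS wording is also ambiguous in the study group, where one treatment could mean acupuncture, clomiphene or either. If it means acupuncture, the entry rule differs between the arms.

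**2. Can a patient know her arm and not start?** Yes. The envelope is opened at enrolment and both treatments begin on day 5 of a bleed. The length of the interval is not given: the visit table shows no randomisation step, and enrolment is not placed within the cycle. Blood is drawn on cycle day 3. If enrolment follows the baseline draw in the same cycle, the gap is about two days; if it precedes the draw, the gap is longer.

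**3. Does the imputation sentence bring non-starters back?** It does not say so. If dropouts include non-starters, that sentence conflicts with the FAS rule. If they do not, non-starters are in no efficacy set.

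**4. The plan's own figures.** The Sample size section gives expected means of 1.0 and 1.6 (difference 0.6), 80% power, alpha 0.05, 37 per group, 15% dropout and 43 per group. No SD is stated, so 37 cannot be reproduced independently, but it can be inverted. A two-sided two-sample t-test with n = 37 per group has 80% power at a standardised difference of 0.660, so the implied SD is 0.6 / 0.660 = 0.91. In the other direction, an SD of 0.90 returns 37 per group. For dropout, 37 × 1.15 = 42.55 gives the stated 43, while 37 / 0.85 = 43.5 gives 44. That difference of one patient per group does not affect this point.

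**5. Illustrative size.** Assumptions, none of them in the protocol: SD 0.91; k of 43 patients in one arm never start; their mean outcome differs from the mean of all randomised patients in that arm by δ = 0.5 or 1 SD (0.455 or 0.91); no matching loss in the other arm. Dropping them moves the arm mean by

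shift = k / (43 − k) × δ

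| k | Calculation, δ = 0.5 SD | Shift | Share of 0.6 | Shift, δ = 1 SD | Share of 0.6 |
|---|---|---|---|---|---|
| 1 | 1/42 × 0.455 | 0.011 | 2% | 0.022 | 4% |
| 2 | 2/41 × 0.455 | 0.022 | 4% | 0.044 | 7% |
| 4 | 4/39 × 0.455 | 0.047 | 8% | 0.093 | 16% |
| 6 | 6/37 × 0.455 | 0.074 | 12% | 0.148 | 25% |

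If δ is measured against the patients who do start, the multiplier is k/43. The top case is then 6/43 × 0.91 = 0.127 (21%).

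**6. Direction.** The plan expects the lower ratio in the study group. Losing study-group patients with high values, or controls with low values, favours acupuncture. The reverse losses work against it. Similar losses in both arms cancel.

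**The case against.** Several counter-arguments carry weight.

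- **The imputation sentence shows an intention to keep leavers in and to disclose withdrawals.** It does, and it should be read together with the FAS definition. It does not override an entry rule stated explicitly elsewhere, so the two need reconciling.
- **Non-starters may be few.** Both arms receive active clomiphene, and participants are infertile women who want to conceive and are suitable for it. This is plausible. The protocol gives no non-starter rate, so the effect may be close to nil.
- **The outcome is a laboratory ratio and data collectors are blinded.** This protects measurement, but not selection into the analysis set.
- **The primary outcome is the change in LH/FSH.** Any difference already present at baseline cancels in a change score. The δ above must therefore be read as a difference in the outcome analysed, and the implied SD may not be the SD of the change.
- **The fix is only partial.** This stands: without an end-of-study sample, a non-starter's outcome is imputed with no data after randomisation.

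Three stronger readings are tempting but unsupported. A reader might infer that patients wait a whole cycle knowing their arm; the protocol never says that treatment begins at the next menses. A reader might infer that the bias favours acupuncture by some particular amount; nothing fixes its direction or size. A reader might also object that neither the full analysis set nor the per-protocol set is named as primary; an article commonly leaves that to the full protocol or the SAP, neither of which is shown, so it is not part of this point.

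**Conclusion.** The contradiction is certain on the text: the set called intention-to-treat excludes randomised patients who received no treatment, and no other defined set includes them. A SAP might add detail, but the protocol itself fixes this definition. Because allocation is known before treatment begins, the exclusion can depend on the arm and can bias the comparison either way.

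The size of any bias is unknown. The range of 0.01 to 0.15 rests on an inferred SD, an assumed 1 to 6 non-starters confined to one arm, and an assumed prognostic difference of 0.5 to 1 SD. It shows that a few exclusions can matter with 43 per arm; it does not predict what will happen. The definition should be corrected, and no sample-size figure changes.

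**What to change.** 1. Define the FAS as all randomised patients, analysed in the arm assigned, whether or not treatment began (86 planned, 43 per group).
2. Seek the end-of-study blood sample from patients who never start. Where it cannot be obtained, apply the planned imputation to them and add a sensitivity analysis that varies the assumed outcome of non-starters in each arm.
3. State in Data collection and management that dropouts include patients who leave before a first treatment, so that the section agrees with the FAS definition.
4. Keep receipt of at least one intervention as the rule for the safety set only.

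The cost is a few sentences and the effort to recall a probably small number of patients. No extra patients are needed and treatment does not change. The downside is that a few outcomes may have to be imputed without any data after randomisation, which is why the sensitivity analysis is needed.

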### Outcome measures

#### Primary outcome

The primary outcome will be the change of LH/FSH. Data will be collected before the start of the study (the baseline assessment) and after 3 menstrual cycle treatments.

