### Sample size

A previous study has found an average LH/FSH ratio for patients with PCOS after true acupuncture treatment of 1.4 [33]. Thus, we expect that the average LH/FSH ratio will be 1.0 in the study group and 1.6 in the control group. Assuming a power of 80% and a significance level of 0.05, 37 participants in each group will be required, as calculated using the *t*-test in G*Power. Based on a 15% dropout rate, 86 patients will be recruited, with no less than 43 participants in each group. Since there is no standard sample size calculation for metagenomic analysis at present, according to most of the studies about gut microbial studies for PCOS [44, 66], of the 86 participants, 10 patients in each group (5 patients with post-intervention serum LH/FSH levels of 1.0–1.5 and 5 patients with serum LH/FSH levels over 1.5) will be selected for metagenomic analysis.

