### Data collection and management

Data collection will be conducted at baseline and post-intervention. Data collectors will record participant data on case report forms (CRFs). All data collectors will receive training on how to administer the SAS and SDS scales. After data collection using CRFs, we will use an electronic database for data entry and management. Two data collectors will perform double data entry, and completed clinical raw data will be forwarded to the supervisor of the project for review. The supervisor will correct any errors and export the data. After confirmation, the database will be locked and undergo statistical analysis. All data will be identified using participant numbers and stored in the database, which will be accessed using a password. The data will be monitored by the ethical review board of the Hospital of Chengdu University of Traditional Chinese Medicine.

The incidence of withdrawal from the study and the withdrawal reasons will be reported. Dropouts will be included in the analysis using modern imputation methods for missing data.

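### The primary comparison uses baseline LH/FSH only by subtraction and lets the data choose between a mean difference and a rank comparison; one prespecified ANCOVA would be more efficient

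*Protocol article*

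**What the plan says.** Primary outcome section: "The primary outcome will be the change of LH/FSH", measured before the study starts and again after three treated cycles. Data collection and management confirms the two time points: "Data collection will be conducted at baseline and post-intervention". Baseline LH/FSH is therefore planned for everyone randomised.

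Statistical methods gives one rule for comparing arms on continuous data: an independent-samples t-test or a Mann-Whitney U "rank sum test according to whether the measurement data show a normal distribution and homogeneous variance". Significance is judged at "0.05 with a two-sided test". The section names no covariate and no transformation.

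Sample size works with levels, not changes. The cited earlier trial supplies a mean only: "A previous study has found an average LH/FSH ratio for patients with PCOS after true acupuncture treatment of 1.4". From it, "we expect that the average LH/FSH ratio will be 1.0 in the study group and 1.6 in the control group". Then: "Assuming a power of 80% and a significance level of 0.05, 37 participants in each group will be required", using a t-test in G*Power. No SD, effect size or baseline–post correlation is given.

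**The concern.** There are three linked weaknesses.

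- **Baseline is used inefficiently.** A change score adjusts for baseline with the slope fixed at 1. When the correlation between visits is below 1 and the variances are similar, that slope is too steep and adds noise. ANCOVA estimates the slope.
- **The effect measure is left to the data.** If the check passes, the primary result is a difference in mean change. If it fails, the result is a rank comparison. These answer different questions. Unequal variance is also a poor reason to move to Mann-Whitney, which is not a clean test of location when spreads differ.
- **The powered variable is not shown to be the analysed one.** The calculation uses average ratios of 1.0 and 1.6, but the test is on the change, whose SD depends on the between-visit correlation.

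At stake is the precision of the main comparison in a trial of 86 patients, and whether the 80% power belongs to the analysis that will be run.

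**Working it through.** **Inputs from the article:** difference in means 1.6 − 1.0 = 0.6; 37 per group; two-sided 0.05; 80% power.

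**Inputs not in the article (assumptions):** the SD, back-solved below; the baseline–post correlation ρ, taken as 0 to 0.7; equal SD at both visits.

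**1. The plan's own figure.** With no SD, 37 per group cannot be reproduced directly. Two-sided noncentral-t power is based on noncentrality 0.6 / (SD × √(2/37)). Solving for 80% gives SD = 0.909, so d = 0.6/0.909 = 0.66. Any SD from about 0.896 to 0.909 leads to 37. Below, 0.909 is taken as the single-visit SD.

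**2. Variances.** With single-visit variance σ²:
- change score: 2σ²(1 − ρ)
- ANCOVA residual: σ²(1 − ρ²)
- ratio, ANCOVA to change: (1 − ρ²) / [2(1 − ρ)] = (1 + ρ)/2

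The ratio is below 1 for every ρ below 1. The change score matches the post-treatment value in variance only when 2(1 − ρ) = 1, that is ρ = 0.5.

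**3. Power at 37 per group** (72 df for change, 71 for ANCOVA). The last column is n per group for 80% power by the normal approximation.

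| ρ | SD of change | ANCOVA residual SD | Variance ratio | Power, change | Power, ANCOVA | n, change / ANCOVA |
|---|---|---|---|---|---|---|
| 0 | 1.285 | 0.909 | 0.50 | 51% | 80% | 73 / 37 |
| 0.3 | 1.075 | 0.867 | 0.65 | 66% | 84% | 51 / 33 |
| 0.5 | 0.909 | 0.787 | 0.75 | 80% | 90% | 37 / 28 |
| 0.7 | 0.704 | 0.649 | 0.85 | 95% | 98% | 22 / 19 |

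**4. The other reading of the SD.** Randomisation makes the expected baseline difference zero, so a difference of 0.6 in post-treatment means is also the expected difference in change. If 0.909 was the SD of the change, the planned t-test has its 80%. ANCOVA still gains: at ρ = 0.5 its residual SD is 0.909 × √0.75 = 0.787, which gives 90% as in the table.

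**5. Skew and the gate.** A normal distribution with mean 1.0 and SD 0.91 puts about 14% of values below zero; with mean 1.6 it puts about 4% there. A ratio of two hormone levels cannot be negative, so right skew at a single visit is plausible if that SD is right. The change itself can be negative, so these figures say nothing direct about its shape.

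As an illustration only, lognormal data were simulated with log SD 0.62, mean ratios 1.0 and 1.6 after treatment, and 37 per group. The gate was taken as Shapiro-Wilk in each arm plus Levene, because the article names no tests. With 3,000 runs per ρ:

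| ρ | Gated test on change | Raw-scale ANCOVA | Log-scale ANCOVA |
|---|---|---|---|
| 0 | 49% | 83% | 89% |
| 0.3 | 63% | 86% | 93% |
| 0.5 | 75% | 90% | 96% |
| 0.7 | 92% | 97% | >99% |

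The gate sent 78% to 91% of these runs to Mann-Whitney. Under no effect, with ρ = 0.5 and 5,000 runs, the gated procedure rejected in 4.9%.

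**The case against.** The strongest reply is that both the SD and ρ are the reviewer's assumptions. The article gives neither, and 0.91 may have been meant for the change, in which case 80% stands. Even on the single-visit reading there is no shortfall at ρ = 0.5, and power is well above target at 0.7. All of that is right. A reader might infer that the trial is underpowered; the document does not support that. It supports only that the 80% has not been tied to the change.

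Two other inferences also go too far. One is that chance baseline imbalance is left uncorrected: a change score does account for baseline, though with a fixed slope. The other is that analysts will pick the test at will, or that false positives are inflated. The selection rule is stated in advance, the Blinding section says statisticians are blinded, and the simulation showed no inflation.

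It can also be said that a condensed article leaves covariates and transformations to the analysis plan. That is a good reason not to fault the lack of a log scale or hospital terms, and both are optional here. It does not remove the point, because the article positively states an unadjusted, data-selected test, and the primary outcome falls under it.

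**Conclusion.** The point stands as a recommendation on efficiency and on fixing the effect measure. That ANCOVA has (1 + ρ)/2 of the change-score variance requires only equal variance at the two visits, and it holds whichever SD was meant. The power figures (51/66/80/95% against 80/84/90/98% at ρ = 0/0.3/0.5/0.7) additionally assume that about 0.91 is the single-visit SD. They are for raw-scale ANCOVA without hospital terms.

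A deficit against the stated 80% needs two things together: the single-visit reading of the SD, and ρ below 0.5. The document establishes neither. Skew is a reasonable expectation under the implied SD, not something the plan states.

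**What to change.** Prespecify one primary analysis: ANCOVA of post-treatment LH/FSH on arm and baseline LH/FSH, reported as the adjusted treatment difference with its 95% CI. Remove the normality and equal-variance gate, and keep Mann-Whitney as a sensitivity analysis. If skew is expected, decide now to use log LH/FSH for both the outcome and the baseline, reported as a geometric mean ratio. The cost of that option is that the result is no longer on the absolute scale of the 0.6 used for sizing.

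In Sample size, state the SD behind 37 per group, whether it describes a single visit or the change, and the correlation assumed if it is a single-visit SD.

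No new data or patients are needed. The trial is registered, open-label and has been running since September 2020, so the change should be made as a dated, documented amendment before database lock.

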#### Secondary outcomes

The secondary outcomes will include changes in biometric features, changes in hormonal parameters/metabolic parameters/inflammatory parameters, changes in Self-Rating Anxiety Scale (SAS) and Self-Rating Depression Scale (SDS) scores, and changes in gut microbiome analysis. Data will be collected before the start of the study and after 3 menstrual cycle treatments.

Biometric features related to obesity, including BMI and waist will be assessed. BMI will be calculated in kg/m^2^. Waist circumference will be measured as the smallest circumference between the lowest rib and the iliac crest [52, 53]. Blood samples to assess hormonal parameters, metabolic parameters, and inflammatory parameters will be collected in the morning after an overnight fast, on day 3 of a menstrual cycle. Sex hormonal parameters will include FSH, LH, total testosterone, progesterone, and estradiol. The adipocyte-secreted hormone will be assessed by leptin, which was discovered in 1994 and can cause abnormal energy homeostasis and profound obesity [54, 55]. Leptin circulates primarily at levels proportional to the amount of adipose tissue, signaling long-term energy storage, and secondarily at levels modified by acute changes in caloric intake [56]. Leptin should decrease weight when circulating at high levels [57], and it plays a clear role in obesity etiology [58]. The metabolic parameters will include fasting blood glucose (FBG), fasting insulin (FINS), homeostatic model assessment for insulin resistance (HOMA-IR), c-peptide release tests, total cholesterol (TC), triglycerides (TG), high-density lipoprotein (HDL-C), and low-density lipoprotein (LDL-C). HOMA-IR will be calculated using the following formula: FBG (mmol/L) × FINS (mIU/L)/22.5 [59]. Inflammatory parameters will include C-reactive protein (CRP), interleukin-6 (IL-6), interleukin-18 (IL-18), and interleukin-22 (IL-22). These cytokines are related to inflammatory cytokines involved in PCOS [60–62]. SAS and SDS scores will be used to assess the patients’ mental health. The Self-Rating Anxiety Scale (SAS) and Self-Rating Depression Scale (SDS) can discriminate anxiety and depression from mood disorder and have been used continuously in research since 1972 [63, 64].

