## Discussion

PCOS is a complex reproductive disorder with multiple manifestations. Women with PCOS are more likely to be overweight [67], and excess weight worsens the features of PCOS [68]. Then, weight management plays an important role in PCOS [69]. Acupuncture is an acceptable adjunct to lifestyle interventions for weight loss in obese women with PCOS [30] and so could improve the treatment of PCOS. There is evidence that acupuncture can improve menstrual frequency and ovulation frequency, decrease the levels of several sex steroids (including testosterone, androsterone glucuronide, androstane-3α, and 17β-diol-3-glucuronide) in women with PCOS, and improve the LH/FSH ratio [27, 28, 33]. Although acupuncture seems to have a beneficial effect on PCOS, evidence for acupuncture’s utility for PCOS is conflicting [70], and the add-on effect of acupuncture for obese women the PCOS has not been studied. Besides, we speculated that the differences in the individual curative effect of acupuncture may explain the inconsistent results, and to the best of our knowledge, no studies have examined the potential mechanism of individual differences in acupuncture’s curative effect in obese women with PCOS. This will be the first trial to compare acupuncture with clomiphene citrate in obese women with PCOS with the aim of exploring the connection between acupuncture and the gut microbiome. On the basis of previous clinical studies and studies on the mechanism of acupuncture, we hypothesize that acupuncture will improve biomarkers and symptoms by regulating the gut microbiome composition of obese women with PCOS. Our findings will add to research on the PCOS phenotype and elucidate the role of the gut microbiome in individual curative effect differences of acupuncture based on metagenomic analysis.

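### One two-sided 0.05 rule covers all tests, so 22 clinical secondary outcomes and an unstated number of correlations can each be declared significant with no adjustment, order or exploratory label; the single primary is unaffected

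*Protocol article*

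**What the plan says.** The protocol article names one primary: "The primary outcome will be the change of LH/FSH" (Primary outcome), and the Sample size section powers the trial on LH/FSH alone.

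The Secondary outcomes section is broad: "The secondary outcomes will include changes in biometric features, changes in hormonal parameters/metabolic parameters/inflammatory parameters", plus the anxiety and depression scales and the microbiome analysis. It then itemises the clinical variables, for example "Biometric features related to obesity, including BMI and waist will be assessed" and "Sex hormonal parameters will include FSH, LH, total testosterone, progesterone, and estradiol".

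Statistical methods compares groups on measurement data by t-test or Mann-Whitney test and adds that "Pearson correlations and Spearman correlations will be used to analyze the correlations between different indicators". It closes with the rule for significance: "All statistical tests will be considered statistically significant at *P <* 0.05 with a two-sided test".

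The article describes the microbiome and mechanism work in exploratory terms. It uses no such terms for the clinical secondaries or the correlations, and it neither ranks them nor adjusts for their number. The Discussion says: "we hypothesize that acupuncture will improve biomarkers and symptoms by regulating the gut microbiome composition of obese women with PCOS".

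**The concern.** How multiple secondary outcomes are handled is often left to a statistical analysis plan, and silence on it would not be a finding. Here the article is not silent: it fixes the threshold for every test. A later plan that adjusted the secondaries, or withheld the word significant from them, would depart from that sentence.

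Applied as written, the rule gives each of a long list of markers its own chance of being declared significant at 0.05. If acupuncture added nothing to clomiphene, one or more markers could still cross the threshold. The text does not say how such a result is to be read, in particular when LH/FSH shows no difference. The correlations raise a parallel problem: chance associations between indicators could be read as mechanism.

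**Working it through.** The article states no family-wise error rate, so there is no figure of its own to reproduce. The check is a count followed by the error rate that the written rule implies.

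**Count of clinical secondaries** (Secondary outcomes section; microbiome analyses left out)

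| Domain | Variables | Number |
|---|---|---|
| Biometric | BMI, waist | 2 |
| Hormonal | FSH, LH, total testosterone, progesterone, estradiol, leptin | 6 |
| Metabolic | FBG, FINS, HOMA-IR, C-peptide release (counted once), TC, TG, HDL-C, LDL-C | 8 |
| Inflammatory | CRP, IL-6, IL-18, IL-22 | 4 |
| Questionnaires | SAS, SDS | 2 |
| **Total** | | **22** |

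LH and FSH make up the primary ratio; without them 20 remain.

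**Expected false positives with no true effect.** 22 × 0.05 = 1.1 (20 × 0.05 = 1.0). This holds whatever the correlation.

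**At least one false positive, independent tests**
- Either direction: 1 − 0.95^22 = 0.676.
- Favourable direction only (0.025 per test): 1 − 0.975^22 = 0.427.
- With 20 variables: 1 − 0.95^20 = 0.642 and 1 − 0.975^20 = 0.397.

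Independence cannot hold exactly, because the article defines HOMA-IR as FBG × FINS/22.5. These figures serve only as upper bounds against positively correlated outcomes.

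**At least one false positive, correlated tests.** The article gives no correlations, so these are assumptions: 22 normal test statistics with a common correlation, critical value 1.96, by simulation.

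| Assumed common correlation | Either direction | Favourable direction |
|---|---|---|
| 0.3 | 57% | 30% |
| 0.5 | 44% | 22% |
| 0.8 | 23% | 12% |

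A structure with correlation 0.3 to 0.7 within domains and 0.1 to 0.2 between them gives 48% to 63% in either direction and 25% to 36% in the favourable direction.

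**Correlation tests.** Neither the number nor the pairs are stated, so no error rate can be computed for what is planned.

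**Effect of an adjustment.** Bonferroni, or Holm's first step, over 22 tests uses 0.05/22 = 0.00227. Under independence the family-wise rate is 1 − (1 − 0.00227)^22 = 0.049; it is about 4.3% at correlation 0.3 and 3.5% at 0.5. The primary test and the sample size do not change.

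**The case against.** The strongest reply is that the sentence only sets a nominal level per test, which is ordinary usage. Each test does have a 5% error rate as stated, and family-wise control of secondaries is normally the business of an analysis plan. The trial also has a clear structure: one named primary, everything else labelled secondary, and a sample size built on the primary.

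Much of this stands. A hierarchy does exist between primary and secondary outcomes; what is missing is any order or label among the secondaries. The primary's error rate is intact. The article promises no family-wise rate, so the percentages describe what the rule implies and do not contradict a stated figure.

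A reader might infer more, and three such readings fail:

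- That a false claim that acupuncture improves biomarkers is likely. Such a claim needs the favourable direction, where the chance is at most 43% and about 30% to 12% under the assumed correlations.
- That one significant marker counts as proof of efficacy. No section says so. The Discussion sentence is a mechanistic hypothesis about the microbiome, not a decision rule.
- That all pairs of indicators will be correlated (253 pairs for 22 secondaries plus LH/FSH, about 12.7 chance hits). The article names no such set, and some pairs are algebraically linked, so they could not all be null. Correlations are also not between-group comparisons and do not bear on efficacy.

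What the reply does not remove is the reach of the rule. It covers all tests, and no wording marks secondary or correlation results as nominal.

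**Conclusion.** The point holds as a defect in how secondary and correlation results are to be declared, not in the primary analysis. Applying the written rule to 22 clinical secondaries yields about 1.1 chance findings when there is no effect. The chance of at least one is about 57% to 23% in either direction and about 30% to 12% in the favourable direction.

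These ranges rest on an assumed common correlation of 0.3 to 0.8, on C-peptide release counted as one outcome, and on one between-group test per outcome. Several C-peptide time points would add tests. The risk of a spurious secondary finding is substantial, and the text as written does nothing to limit how such a finding is presented. The primary conclusion and the sample size are unaffected.

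**What to change.** In Statistical methods, replace the closing significance rule with wording to this effect:

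> The comparison of change in LH/FSH is the only confirmatory test and uses a two-sided level of 0.05. Secondary outcomes and correlation analyses are exploratory. They are reported as estimates with 95% confidence intervals and nominal P values, and cannot support a claim of efficacy if the primary test fails.

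If the sponsor wishes to claim any secondary outcome, a short list should be named in advance and tested by Holm's method or in a fixed order, only after the primary test succeeds. If correlations are to be more than descriptive, the pairs should be named in advance and the false-discovery rate controlled over that set.

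The change is wording only: no patient, visit or assay is added. The sponsor gives up the option of presenting an isolated P<0.05 on a secondary marker as a confirmed effect.
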